### Recruitment

Eligible participants will be contacted via telephone calls or information letters from the Units of Paediatric Oncology of the ‘Virgen de las Nieves’ (Granada) and ‘Reina Sofía’ (Córdoba) University Hospitals in Southern Spain. A short study information brochure will be used in routine check-ups. A meeting will be held with potential participants and parents/tutors to carefully inform about the benefits and risks of the study, and researchers will answer any question that they may have. Then, informed consents will be given, and participants will have 15 days to send it to the researchers. A hotline will be available to clarify remaining questions about the study. Those who do not react to the study invitation will be followed up via phone call at the end of these 15 days in order to check if they wish to participate. All participants will sign the informed consent before their visit to the iMUDS.

### Randomization and blinding

Randomization to an intervention group (online exercise programme, IG) or control group (no treatment, CG) will be performed by an external partner ([name]) who is independent of the participant recruitment and enrolment process, stratified by age and sex. Each participant will be provided a uniform (0, 1) random number using SAS software, version 9.1 (SAS Institute Inc), within their respective age and sex group. Assignments will be blinded to the assessors until all tests are completed. For feasibility reasons, the study will probably be conducted in two waves of 58 children at most.

### Sample size

We have used femoral neck aBMD as the outcome to calculate the sample size, since it is a key variable in the diagnosis of osteoporosis. Since the study will include children and adolescents (6–18 years), the sample size has been calculated taking into account that sub-group analysis by age groups (6 to 11 years and 12 to 18 years) may be required. Based on an expected effect size of 0.25 for the change in femoral neck aBMD, an α level of 0.05 and a power of 80%, a minimum of 116 participants will be required (IG = 58 and CG = 58). This includes a 20% extra for occasional losses and refusals and 10% for multivariable analyses. Calculations have been obtained using G*Power (v.3.1.9.2) with analysis of variance: repeated measures (within-between interactions) for 2 groups (between factors) and 2 time points (pre, post, within factors). A correlation between measures of 0.7 has been assumed, which is achievable when measuring bone outcomes [16].

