## Background

Owing to major advances in cancer screening and treatment over the last 30 years, cancer survival has improved dramatically. In Europe, the paediatric cancer incidence increases annually by 0.54% in children (0–14 years) and by 0.96% in adolescents (15–19 years), although it seems that the incidence in adolescents is decelerating [1]. Nevertheless, the 5-year survival rate is now at 77.9% for children and 79% for adolescents and young adults (20–39 years) [2, 3]. Unfortunately, the treatment of paediatric cancer by means of radiation, chemotherapy and/or surgery is associated with various late effects (e.g. impaired growth, musculoskeletal sequelae, cardiopulmonary compromise and secondary malignancy) [4–6], predisposing paediatric cancer survivors to disabling conditions [4]. Furthermore, paediatric cancer treatment has been documented to have an effect on emotional well-being and quality of life, with survivors reporting anxiety, depression and post-traumatic stress [7, 8].

Paediatric cancer is a life-threatening condition that also occurs during the period of bone development and strengthening. Gonadal failure following to pelvic radiation or gonadotoxic chemotherapy and hypothalamic pituitary dysfunction by means of cranial radiation can adversely affect areal bone mineral density (aBMD), increasing osteoporosis risk later in life [9, 10]. In addition, direct radiation to bone not only causes hypovascularity but has a direct cytotoxic effect on the epiphyseal chondrocytes [11]. Observational studies have found low aBMD during and after cancer treatment to be associated with increased fracture risk (80% increase for every 1 SD reduction in lumbar spine aBMD Z-score) [12–15], which can lead to a higher risk of osteopenia and osteoporosis in adulthood and finally, disability [16, 17]. Moreover, data from a review showed that up to 68% of paediatric cancer survivors presented moderate-to-severe aBMD deficits (Z-score < − 1), while up to 46% had severe aBMD deficits (Z-score < − 2) [18].

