### Exercise and bone health

Exercise contributes to the development of bone mass in youths due to its association with increases in lean mass [31, 32]. Larger muscles exert greater forces on the bones, which will adapt and therefore improve their strength [33]. Furthermore, plyometric jump training is one of the best methods to improve bone health since the impacts produced against the ground will cause higher forces on the bones [34]. A recent systematic review has shown that plyometric jump training causes improvements in bone mineral content (BMC), aBMD and structural properties in children and adolescents [35]. More specifically, an 8-month jumping intervention (~ 3 min/day) improved bone mass in the proximal femur in pubertal children [36]. Mackelvie et al. [37] showed that a 7-month jumping intervention (10 min, 3 times/week) enhanced bone mass in the femoral neck and lumbar spine in pubertal girls. Additionally, Vlachopoulos et al. [38, 39] found that a 9-month jumping intervention (10 min, 3 to 4 times/week) improved bone outcomes in adolescent males participating in non-osteogenic sports and with poorer bone health.

A similar effect might be seen in survivors of paediatric cancer. A randomized controlled trial (RCT) in children with acute lymphoblastic leukaemia showed that resistance exercise was unsuccessful in preventing the reduction in aBMD [40]. However, the intervention (duration, load) was not properly described. A RCT focusing on low-magnitude, high frequency mechanical stimulation seemed to improve total body aBMD in paediatric cancer survivors, while a reduction was observed in the placebo group [41]. In a recent study in children with cancer, the exercise programme was not successful in improving aBMD nor other factors such as physical function or health-related quality of life [42]. This was because exercise requires of certain intensity to modify these factors and this could not be achieved during treatment due to the child’s responses to the treatment and disease. Considering the gap in the literature, and taking into account the Exercise Guidelines for Cancer Survivors [43, 44], it is crucial to develop and implement feasible exercise programmes focused on improving bone health into survivorship.

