### Statistical analysis

All variables will be checked for normality using both statistical and graphical methods. Results will be presented as frequencies and proportions with 95% confidence intervals for categorical variables and mean (standard deviation) or median (range) for continuous variables. A descriptive analysis of the participants characteristics will be performed as soon as the baseline assessments are completed. This cross-sectional analysis will show the comparability of IG and CG and the need for adjustment when between group comparisons are done.

General Lineal Models will be used to examine the training effects [time (pre-post 9-month intervention) x group interaction] on the primary and secondary outcomes. Change in bone outcomes will be used as age and sex-adjusted z-scores. The baseline level of each outcome variable will be entered as covariate. Effect sizes will be reported. Multiple imputation methods and sensitivity analysis (i.e. propensity score) will be performed to handle missing data and appreciate the potential influence of missing responses. Finally, in the event of possible dropouts, a statistical analysis will be carried out by protocol and intention to treat.

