### Secondary outcomes

#### Anthropometric measurement, body composition and somatic maturation

Body mass (kg) will be measured with an electronic scale (SECA 861, Hamburg, Germany) with an accuracy of 100 g. Height (cm) will be measured by using a precision stadiometer (SECA 225, Hamburg, Germany) to the nearest 0.1 cm. Body mass index (BMI) will be calculated as body mass (kg)/height (m^2^), and the participants will be classified into BMI categories according to sex- and age-specific cut offs [80].

In addition to DXA measurements, a bioimpedance scale (Tanita BC-418 MA; Amsterdam, The Netherlands; range: 2–200 kg; precision: 0.1 kg; body fat percentage increments: 0.1%) will estimate the percentage of body fat of the participants. The assessment will be carried out in fasting state according to the manufacturer’s instructions. Despite the measured error, bioelectrical impedance analysis will be used to assess body fat as it is considered a practical method in addition to DXA [81].

Somatic maturation will be assessed using the prediction of years from peak height velocity using validated algorithms for children [82].

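### The baseline maturity measure has no stated role in the analysis: prespecify it as a covariate for the bone outcomes instead of letting observed imbalance decide

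*Protocol article*

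**What the plan says.** All references are to the protocol article.

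- **Statistical analysis.** "Change in bone outcomes will be used as age and sex-adjusted z-scores". The only covariate named is the baseline level of the outcome. A descriptive comparison of the arms, made once baseline assessments are complete, is to show whether other adjustment is needed.
- **Anthropometric measurement, body composition and somatic maturation.** "Somatic maturation will be assessed using the prediction of years from peak height velocity". This is listed with the secondary outcomes, which are assessed at baseline, so a T0 value will exist. No section makes it a stratum, covariate or effect modifier.
- **Randomization and blinding.** Allocation is stratified by age and sex. No age cut is given there.
- **Sample size.** The section raises this possibility: "sub-group analysis by age groups (6 to 11 years and 12 to 18 years) may be required". The reason given is the wide age range; maturity is not mentioned. The same section adds 10% to the sample for multivariable analyses.
- **Background.** Impaired growth is listed among the late effects of treatment. The causes given for low aBMD are: "Gonadal failure following to pelvic radiation or gonadotoxic chemotherapy and hypothalamic pituitary dysfunction by means of cranial radiation".
- **Exercise and bone health; Discussion.** Earlier jumping trials are described partly by pubertal stage. One, for example, "improved bone mass in the proximal femur in pubertal children"; others are in pubertal girls and prepubertal boys.

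**The concern.** Eligibility runs from 6 to 18 years, so the sample spans growth and puberty. An age- and sex-adjusted z-score places a child against the average for that age and sex. It does not distinguish an early maturer from a late one of the same age and sex, and that difference stays in the residual. By the Background's own account of growth and endocrine damage, it may be larger in these children than in healthy ones.

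The plan collects a measure aimed at this variation, yet its only stated route to further adjustment is how alike the arms look at baseline. In a randomised trial that is a weak criterion. A prognostic covariate reduces residual variance whether or not the arms happen to differ on it, so the rule would leave maturity out whenever the arms looked similar. At stake is the precision of the bone comparisons and, secondarily, how any age-subgroup result may be read.

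**Working it through.** **1. The plan's own figure.** Inputs from Sample size: effect size 0.25 (read as Cohen's f), α 0.05, power 80%, correlation 0.7, two groups, two times. With noncentrality λ = f²·N·m/(1 − ρ), where m = 2 and the degrees of freedom are 1 and N − 2, these give 22 evaluable children in total (power 0.82). Allowances of 20% and 10% give 22 × 1.2 × 1.1 = 29; two age bands give 2 × 29 = 58. The stated 116 is reached only as 4 × 29, so it is not reproduced from the text. That is a separate matter with no bearing on this point. Below, 116 is simply the enrolment total, and 116/1.32 ≈ 88 the evaluable number.

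**2. What adjustment could gain.** If baseline maturity explains a further share R² of the residual variance, beyond the z-score scale and the baseline outcome, that variance falls to (1 − R²) and the gain is equivalent to multiplying the sample by 1/(1 − R²). The documents give no R², so the range is an assumption.

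| Assumed extra R² | 1/(1 − R²) | 116 children perform like |
|---|---|---|
| 0 | 1.00 | 116 |
| 0.10 | 1.11 | 116/0.90 = 129 |
| 0.20 | 1.25 | 116/0.80 = 145 |

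**3. What adjustment costs.** For two groups and p normally distributed covariates, chance imbalance multiplies the expected variance of the adjusted difference by (n − 3)/(n − 3 − p). With n = 88, going from one covariate to two multiplies it by (85/83)/(85/84) = 84/83 = 1.012. The covariate therefore pays for itself once its extra R² exceeds about 1/84 = 1.2%.

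**4. Why the age subgroups cannot be read as maturity effects.** Let a share q of each age band belong to the other maturity stage. A difference in effect between stages, seen through the age bands, shrinks by (1 − 2q). The documents do not give q, so it too is assumed. Take 88/4 = 22 children per arm and band, and an effect of 1.0 SD in one stage (what f = 0.25 implies here, since matching λ to the two-sample form gives 4f) and 0 in the other. The SD of change is √(2(1 − 0.7)) = 0.775, and the standard error of the subgroup contrast is 0.775 × √(4/22) = 0.330. Power is Φ((1 − 2q)/0.330 − 1.96).

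| q | Contrast seen (SD) | Power |
|---|---|---|
| 0 | 1.0 | 0.86 |
| 0.1 | 0.8 | 0.68 |
| 0.2 | 0.6 | 0.44 |
| 0.3 | 0.4 | 0.23 |

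Modest disagreement between age and stage would thus hide much of a real maturity difference. A null age-subgroup result would say little about maturity.

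**The case against.** The strongest reply is that this is silence, not error. A journal article need not list every covariate; the text leaves adjustment open and reserves 10% of the sample for multivariable analyses, and an unseen analysis plan may use the maturity measure. This stands against any claim that the measure will not be used. It does not dispose of the point, because the article does state a criterion for further adjustment, and that criterion is observed comparability.

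A second reply is that the measure may be poor. It is a prediction, and nothing in the article shows it to be accurate in survivors. If impaired growth weakens age as a guide to maturity, it may weaken a growth-based prediction too. Somatic maturation is also not the pubertal stage by which the cited trials are described. This stands, and it is why the gain cannot be promised and why replacing the age bands with a peak-height-velocity split would be a preference, not a correction.

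Three stronger readings are tempting and unsupported:

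- *The age bands are a proxy for maturity, so the subgroups answer the wrong question.* Sample size never says so. The bands are conditional and answer a question about age. The cut at 12 appears only there, not in the stratification or the z-scores.
- *The protocol says treatment disturbs puberty.* The Background ties gonadal and pituitary damage to aBMD and lists impaired growth; it does not mention puberty. Disturbed maturation is a reasonable inference only.
- *The main result is biased.* Random allocation, stratified by age and sex, protects it, and omitting a prognostic covariate does not change that.

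**Conclusion.** The point holds in a limited form. Maturation at a given age and sex is left in the residual, the collected baseline measure of it has no stated role, and the rule for further adjustment depends on chance imbalance. The consequence is a possible loss of precision on the bone outcomes, not bias. Its size is unknown: 11% to 25% more children is what an assumed extra R² of 10% to 20% would be worth, and the true value could be near zero. Against that, the expected cost is about 1% in variance on 88 evaluable children. This is a low-cost improvement worth making before outcome data are seen; it is not a threat to the validity of the trial.

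**What to change.** In Statistical analysis, state that T0 predicted years from peak height velocity will enter the model as a fixed covariate for all bone outcomes, alongside the baseline outcome and regardless of the observed comparison of the arms. Years from peak height velocity is age minus age at peak height velocity, so over 6 to 18 years much of its spread is age. Carrying the stratification factors, age and sex, in the model as well would let its coefficient reflect maturity at a given age.

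Keep the optional 6–11 and 12–18 subgroups, but say that they concern age and will not be interpreted as maturity effects. If maturity as an effect modifier is of interest, add one prespecified, exploratory group-by-maturity interaction.

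Cost: wording only, with no new measurement or visit. The maturity covariate uses one degree of freedom, and age and sex a few more if added. The remaining downsides are a gain of unknown size and reliance on a prediction whose accuracy in survivors the documents do not establish, which the report should acknowledge.

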**Methods:**

A minimum of 116 participants aged 6 to 18 years will be randomized into an intervention (*n* = 58) or control group (*n* = 58). The intervention group will receive an online exercise programme and diet counselling on calcium and vitamin D. In addition, five behaviour change techniques and a gamification design will be implemented in order to increase the interest of this non-game programme. The control group will only receive diet counselling. Participants will be assessed on 3 occasions: 1) at baseline; 2) after the 9 months of the intervention; 3) 4 months following the intervention. The primary outcome will be determined by dual energy X-ray absorptiometry (DXA) and the hip structural analysis, trabecular bone score and 3D-DXA softwares. Secondary outcomes will include anthropometry, body composition, physical fitness, physical activity, calcium and vitamin D intake, blood samples, quality of life and mental health.

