## Methods/ design

### Study design

This protocol is reported based on Standard Protocol Items: Recommendations for Interventional Trials (SPIRIT) guidelines [45]. The iBoneFIT study is a multi-centre, parallel groups RCT (1:1) designed under the equivalence basis and registered in isrctn.com (Reference: isrctn61195625, 2 April 2020). Eligible participants from two paediatric oncology units of Southern Spain will be contacted, informed, and if consenting, enrolled into the study after a meeting (T_− 1_) (see recruitment section). Then, randomization will be performed by an external partner who is independent of the participant recruitment and enrolment process (see randomization section). Assessments will be conducted at baseline (T_0_) and after nine (T_1_) and thirteen (T_2_) months in the Sport and Health University Research Institute (iMUDS, University of Granada). After finishing the study, participants in the control group will be offered the same online exercise programme. A graphical description of the study design is shown in Fig. 1.

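### The printed inputs and allowances give a total of about 57 to 63, not 116, and the metric of the 0.25 effect size is not stated

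*Protocol article*

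**What the plan says.** All the inputs stand in the Sample size section of the protocol article:

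- Effect: "Based on an expected effect size of 0.25 for the change in femoral neck aBMD". The metric is not named.
- Error rates: "an α level of 0.05 and a power of 80"%.
- Correlation: "A correlation between measures of 0.7 has been assumed".
- Routine: G*Power, "analysis of variance: repeated measures (within-between interactions) for 2 groups (between factors) and 2 time points (pre, post, within factors").
- Allowances: "This includes a 20% extra for occasional losses and refusals and 10% for multivariable analyses".
- Age groups: the calculation took into account that "sub-group analysis by age groups (6 to 11 years and 12 to 18 years) may be required".

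The result is a minimum of 116, 58 per arm, and the abstract repeats it: "A minimum of 116 participants aged 6 to 18 years will be randomized". The section gives no base number before inflation and does not say how the age groups entered. The Statistical analysis section plans general linear models with the baseline value as covariate, and uses age- and sex-adjusted z-scores for change in bone outcomes.

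**The concern.** The section names the software routine and prints every input that it needs, so a reader can rerun it. Rerunning it does not lead to 116, even after every allowance in the text.

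The label on the effect size adds a second difficulty. An effect size of 0.25 for a change can be read as a quarter of a standard deviation. The named routine takes Cohen's f, and there 0.25 is a much larger difference. The two readings put the power of the same 116 children on opposite sides of 80%. How a null result on femoral neck aBMD should be read depends on which one is meant: it would be strong evidence against a very large effect, or weak evidence about a modest one.

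**Working it through.** **1. The named routine.** Inputs from the Sample size section: k = 2 groups, m = 2 time points, ρ = 0.7, α = 0.05, and 0.25 entered as f. With G*Power's default effect-size option the noncentrality is λ = f²·N·m/(1 − ρ), with 1 and N − 2 degrees of freedom.

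- N = 20: λ = 0.0625 × 20 × 2 / 0.3 = 8.33; power 77.9%.
- N = 22: λ = 0.0625 × 22 × 2 / 0.3 = 9.17; power 82.1%.

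The smallest balanced total is 22, that is, 11 per arm. N is the total over both arms.

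**2. The stated allowances.** The text does not say whether they are added, compounded or applied by division.

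| Step | × 1.30 | × 1.32 | ÷ 0.72 | ÷ 0.70 |
|---|---|---|---|---|
| 22 in total | 28.6 | 29.0 | 30.6 | 31.4 |
| 22 in each of two age groups (44) | 57.2 | 58.1 | 61.1 | 62.9 |

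The plan's 116 is about twice the second row.

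**3. Can 116 be recovered?** One route is to use 22 in each of the four arm-by-age cells: 22 × 4 × 1.32 = 116.2, or 22 × 1.3 = 28.6, rounded to 29, and 29 × 4 = 116. This would treat a total as a per-arm number. It is an inference, since the text shows no such step.

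G*Power's other two effect-size options do not recover it either. With λ = f²·N the required total is 128, and with λ = f²·(N − 2) it is 130, both before any allowance. Under those options 116 gives 76% and 75%.

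**4. Power of the stated size at f = 0.25 (default option).**

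- N = 116: λ = 48.3; power above 99.9%.
- One age group of 58 (assuming an even split by age): λ = 24.2; power 99.8%.
- One age group with 44 evaluable: λ = 18.3; power 98.7%.

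**5. What f = 0.25 means here.** In a 2 × 2 interaction the cell effects are ±Δ/4, where Δ is the between-arm difference in change. So f = Δ/(4·SD), and Δ = 4 × 0.25 = 1.0 SD of aBMD. The SD of the change is √(2 × (1 − 0.7)) = 0.775 SD, so Δ is 1/0.775 = 1.29 SD of the change score.

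**6. If 0.25 were a standardised mean difference.** Two-sided t test, 58 per arm, noncentrality (Δ/σ)·√(58/2), where √29 = 5.385:

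- 0.25 SD of aBMD, change score (σ = 0.775): 0.323 × 5.385 = 1.74; power 41%.
- 0.25 SD of aBMD, baseline-adjusted (σ = √(1 − 0.49) = 0.714): 0.350 × 5.385 = 1.89; power 46%.
- 0.25 SD of the change: 0.25 × 5.385 = 1.35; power 27%.

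With 46 evaluable per arm (58 × 0.8 = 46.4) these fall to 33%, 38% and 22%.

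**7. Difference detectable with 80% power, baseline-adjusted (σ = 0.714).**

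- 58 per arm: 0.37 to 0.38 SD (0.375).
- 46 evaluable per arm: 0.42 SD.
- 23 evaluable per arm within one age group (29 × 0.8 = 23.2): 0.60 SD.

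**The case against.** **The four main inputs are not claimed to give 116 by themselves.** The section says that the figure also covers losses, multivariable analyses and possible age-group analyses. This stands, and it is why the fair comparison is 57 to 63 against 116, not 22 against 116.

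**In the metric that the routine takes, the error makes the trial larger than needed, not smaller.** This also stands, and some excess over 80% overall is intended because of the age groups. It does not explain the figure, since each age group alone would have about 99% power.

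**The full protocol may show the base number and the multiplier.** It may, and the article need not print them. But the article does print a complete set of inputs and a result, and the two do not agree.

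A reader might go further and infer that the trial is underpowered. The document does not support this. Power below 50% follows only if 0.25 is a standardised mean difference. The text never says so, and it names a routine that takes f. Nor does the text show that the authors mistook a total for a per-arm number. That route is plausible, but the rounding and inflation that lead to 116 are not unique.

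**Conclusion.** The point holds in this form: 116 as the minimum for 80% power does not follow from the printed inputs. The named routine, with every stated allowance and each age group powered separately, gives about half that number. None of the three G*Power effect-size options gives 116.

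At f = 0.25 the stated 80% understates the design's power. That f is, however, a difference in change of a full SD of aBMD, and the wording does not tell the reader so. The unnamed metric is the more consequential part, because power at 58 per arm runs from 27% to above 99.9% depending on how 0.25 is read.

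These results rest on r = 0.7 as stated, a two-sided 5% test (equivalent to the 1-df F test), and an even split between the age groups. The detectable differences also assume that r = 0.7 holds on the z-score scale used in the analysis; the document gives no correlation or SD for that scale.

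**What to change.** Keep 116 and rewrite the Sample size paragraph:

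- State whether 0.25 is Cohen's f. If so, say that it corresponds to a between-arm difference in change of 1.0 SD of aBMD (1.29 SD of the change score).
- Give the base number from the routine, the age-group multiplier, and how the 20% and 10% were applied. Correct the stated minimum or the stated power so that they agree.
- Give the difference that 116 can detect with 80% power under the baseline-adjusted model: about 0.37 to 0.38 SD with 58 per arm, 0.42 SD with 46 evaluable per arm, and 0.60 SD with 23 evaluable per arm in one age group. Mark these as conditional on r = 0.7 on the analysed scale.

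The cost is one reworded paragraph, with a matching change in the abstract if it is to keep calling 116 a minimum. No extra participants are needed. The downside is that a stated detectable difference of 0.37 to 0.60 SD may look less favourable than a bare effect size of 0.25.
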